## **7.6 Patient treatment**

Irrespective of their randomization, all patients will receive Standard of Care treatment for sepsis, according to the Surviving Sepsis Guidelines (27), including volume resuscitation, administration of vasopressors, antibiotic therapy, hemodynamic monitoring, nutrition, organ support e.g. mechanical ventilation, corrective measures for metabolic abnormalities, and renal replacement therapy, when appropriate.

### **7.6.1 Concomitant medication**

Any medication or treatment required for the welfare and health of the patients enrolled in the study will be administered at the investigator's discretion. All such concomitant medications shall be reported on the CRF during the patient's stay in ICU i.e. from the signature of the discharge from ICU.

Vasopressin and corticosteroids for the treatment of septic shock are not allowed in the study. In patients without pre-existing chronic corticosteroid treatment, corticosteroids are not allowed in the study.

### **7.6.2 Standard of Care group (SOC)**

Patients randomized into the SOC group will receive Standard of Care treatment for sepsis, according to the Surviving Sepsis Guidelines (see above) (27).

### **7.6.3 oXiris™ treatment group**

#### Vascular access

In the oXiris™ group, patients will receive extracorporeal therapy over a venous double-lumen catheter, inserted through the jugular, subclavian or femoral vein. The catheter will be inserted by a trained physician according the guidelines for performing ultrasound guided vascular cannulation (28).

#### Priming of the circuit

Although the oXiris™ membrane is pre-heparinised, it possesses residual capacity for the adsorption of heparin.

Therefore, in order to saturate the membrane, the oXiris™ set is to be rinsed with a 2-Liter priming solution containing 5000 IU/L of unfractionated heparin.

For patients with bleeding risk: once priming is complete, the set blood circuit still contains heparinised solution. Depending on an individual patient's bleeding risk, the physician must decide if additional priming using 500 ml of a non-heparinised solution is necessary.

#### Anticoagulation strategy

Heparin will be used as an anticoagulant for the extracorporeal circuit except for high bleeding risk patients, for whom no anticoagulant will be used. The heparin dose is adjusted to achieve an anti-Xa Level of 0.3-0.5 according to our CRRT SOP.

#### Study treatment duration

The oXiris™ treatment will be applied during 48 hours of treatment i.e. two (2) oXiris™ sets each one used for 24 hours.

#### oXiris™ set change

The oXiris™ set will be changed every 24 hours. The filter change should be done within a 30-45 min time frame.

#### Treatment parameters

Mode: CVVHDF: 20% diffusion-80% convection

Dose: 35 ml/h/kg\*

Reinfusion: 50% Predilution, 50% Postdilution

Blood flow rate (Qb): 150 ml/min at least.

Filtration Fraction should be inferior to 15%.

Once hemodynamic stabilization is achieved, fluid overload should be managed according to the patient clinical needs.

\*prescribed dose to secure a delivered dose of min 25ml/h/kg

#### Cessation of study treatment with oXiris™

The use of oXiris™ set cannot be extended beyond the 48 hours treatment period.

If a patient requires renal replacement therapy beyond the 48 hours study treatment period, he/she will be treated with the usual CRRT set (see below).

### **7.6.4 Toraymyxin™ treatment group**

#### Vascular access

In the Toraymyxin™ group, patients will receive extracorporeal therapy over a venous double-lumen catheter, inserted through the jugular, subclavian or femoral vein. The catheter will be inserted by a trained physician according the guidelines for performing ultrasound guided vascular cannulation (28).

#### Priming of the circuit

The Toraymyxin™ filter is to be rinsed with a 4-liter priming solution followed by 500 ml of heparinised saline solution (4U/ml).

#### Anticoagulation strategy

Heparin 8IU/kg will be administered as maintenance. The maximum maintenance dose allowed for any patient is 2000U/hr. In patients with a high risk for bleeding, no anticoagulant will be used. The heparin dose is adjusted to achieve an ACT of 150 to 180s and an anti-Xa Level of 0.3-0.5 according to our CRRT SOP.

#### Study treatment duration

Patients randomized to the Toraymyxin™ group will be treated for 2 sessions lasting 2 hours each, with an interval of 24 hours after the treatment initiation between the 2 sessions, according to the EUPHAS trial (16).

#### Cessation of study treatment with Toraymyxin™

The use of Toraymyxin™ cannot extend beyond the 24 hour treatment period.

If CRRT is needed, the hemofiltration is performed with the MultiFiltrate™ (Fresenius) and AV1000S haemofilter or the Prismaflex®-system and the Prismaflex ST150 haemofilter according to our SOP. During the treatment period with the Toraymyxin™ filter the CRRT is stopped.

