### 3 Study Flow Chart

#### STUDY FLOW CHART

| Study Periods                                           | Screening & Enrolment | Treatment start | oXiris™ Treatment period 48hrs (2x24h) | Toraymyxin™ and/or SOC Treatment period (2x2h and/or SOC) | Follow up 72hrs | Outcome D28 ± 7days |
|----------------------------------------------------------------|----------------------------------|------------------------|-----------------------------------------------|------------------------------------------------------------------|------------------------|----------------------------|
| Study visits                                            | V1                        | V2              | V3+ V4                                 | V3+ V4                                                    | V5              | V6                  |
| Procedures                                              |                                  |                        |                                               |                                                                  |                        |                            |
| Demographics                                                   | x                                |                        |                                               |                                                                  |                        |                            |
| Medical History                                                | x                                |                        |                                               |                                                                  |                        |                            |
| Infection site, type of infection, documented microbial agents | x                                |                        |                                               |                                                                  |                        |                            |
| Antibiotic therapy                                             | x                                |                        |                                               |                                                                  |                        |                            |

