### **7.9.3 Visit 3 (24 hours) and Visit 4 (48 hours): Treatment period**

- EAA measurement
- IL-6 and HMGB1
- PCT, Lactate, pH
- SOFA score
- Catecholamine doses: Epinephrine, norepinephrine, dobutamine dose
- Volume requirement
- Hemodynamic parameters: MAP, CVP, HR, CO, ELWI, PVPI
- Ventilation parameters: SaO2, FiO2, SvO2
- Urine output (ml/d)
- AE/SAE
- In the SOC with oXiris™ treatment and SOC with Toraymyxin™ treatment groups:
  - Date and time of initiation and termination of each treatment, anticoagulation usage
  - Documentation of achievement of the treatment period or reason for premature disconnection.
- In the SOC treatment group:
  - If renal replacement therapy has to be performed: type of RRT, type of membrane, treatment conditions, duration, and anticoagulation.

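### The Toraymyxin schedule and its time limit contradict each other: a second 2-hour session starting 24 h after initiation ends at about 26 h, but use may not go beyond 24 h

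*Protocol*

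**What the plan says.** All the rules for this arm stand in protocol section 7.6.4. Under Study treatment duration, patients receive "2 sessions lasting 2 hours each, with an interval of 24 hours after the treatment initiation between the 2 sessions". Under Cessation of study treatment, the limit reads: "The use of Toraymyxin™ cannot extend beyond the 24 hour treatment period". The same paragraph then says that CRRT is stopped during the treatment period with the filter.

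Two other places describe the course. The flow chart in section 3 has a column headed "Toraymyxin™ and/or SOC Treatment period (2x2h and/or SOC", set against visits 3 and 4. The heading of section 7.9.3 is "Visit 3 (24 hours) and Visit 4 (48 hours): Treatment period". That section asks the CRF to record the start and end time of each treatment, and whether the treatment period was achieved or why treatment was disconnected early.

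On anticoagulation, section 7.6.4 says: "Heparin 8IU/kg will be administered as maintenance". The next sentence is: "The maximum maintenance dose allowed for any patient is 2000U/hr". The dose is then adjusted to clotting-time and anti-Xa targets under a local procedure.

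**The concern.** Two rules under neighbouring headings of one section cannot both be followed as written. A second session that starts 24 h after initiation cannot also fall within a 24-hour limit on use. Section 10 forbids deviations from the plan except in emergencies, and section 14.1 has the monitor verify compliance. A planned session that breaks a stated limit therefore creates a question for every patient in this arm who receives the full course.

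The same loose term is used elsewhere. The CRF item on achieving the treatment period needs a definition of that period, and the document describes it as 24 hours in one place, as two 2-hour sessions in another, and across the 24 h and 48 h visits in a third. The CRRT instruction rests on the term too. With 10 patients to be analysed per group (section 7.7), this comparator needs one clear definition of a completed course.

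**Working it through.** **Inputs, all from the protocol**

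- Sessions: 2, each of 2 h (section 7.6.4, Study treatment duration).
- Start of session 2: 24 h, counted from treatment initiation (same place: "with an interval of 24 hours after the treatment initiation between the 2 sessions").
- Limit on use: 24 h (section 7.6.4, Cessation of study treatment).

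**Timeline**

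- Session 1: 0 h to 0 + 2 = 2 h.
- Session 2: 24 h to 24 + 2 = 26 h.
- Overrun: 26 − 24 = 2 h, which is the whole of session 2.
- Planned exposure: 2 × 2 = 4 h. Exposure within the limit: 2 h, or 2/4 = 50%.
- Latest start that would let session 2 end within the limit: 24 − 2 = 22 h. The duration paragraph does not provide for that start.

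**Comparison with the oXiris arm**

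Section 7.6.3 gives two sets of 24 h each, 2 × 24 = 48 h, and a limit of 48 h. On nominal set time, leaving aside the minutes needed for the set change, schedule and limit agree. The same check fails for Toraymyxin.

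**Is there an exemption elsewhere?**

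| Place | How the Toraymyxin period is described |
|---|---|
| 7.6.4, Study treatment duration | Two 2-h sessions, second at 24 h |
| 7.6.4, Cessation of study treatment | 24 hours, not to be exceeded |
| Section 3, flow chart | 2 × 2 h, under visits 3 and 4 |
| 7.9.3, heading | Visits at 24 h and 48 h, both in the treatment period |

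No section says that the 24 hours limits only the start of the last session, and none exempts session 2.

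**Effect on the CRRT instruction**

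If the treatment period means the time the filter is running, CRRT is off for 2 × 2 = 4 h in total. If it means the 24-hour period named in the same paragraph, the text describes something different. The first may be the more natural reading, but the document does not state it.

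**Heparin**

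The maintenance figure is per kg with no time unit. The maximum is per hour with no weight unit. The two cannot be compared unless a time unit is assumed.

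**The case against.** The best defence is that the limit is loosely worded and nobody would be misled. The duration paragraph says plainly: "Patients randomized to the Toraymyxin™ group will be treated for 2 sessions lasting 2 hours each". The flow chart repeats it, and section 7.9.3 places the treatment period across two visits. The limit may simply refer back to the 24-hour schedule just described, as the oXiris limit refers to its own planned course. The CRF also records start and end times, so a patient who had one session could be identified.

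Much of this stands, and it rules out several stronger readings that a reader might infer:

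- *That the arm has no defined course, or that the two centres would split between one session and two.* The flow chart and the duration paragraph both point to two sessions. Nothing shows that a centre would give one, so halved exposure is a literal consequence of the limit and not an expected outcome.
- *That session 2 might run from 26 h to 28 h.* This counts the interval from the end of session 1, whereas the text counts it from initiation.
- *That the heparin figures conflict.* IU and U are the same unit for heparin, and a weight-based dose can sit under an absolute hourly maximum. If the maintenance figure is assumed to be hourly, the maximum equals it only at 2000 / 8 = 250 kg, but that does not make the maximum idle. The dose is titrated, so the maximum can apply at lower weights.
- *That the order of the 24 h blood sample and session 2 is an error.* Section 7.8.2.4 leaves sampling details to a study-specific procedure. Endotoxin activity at 24 h is neither the primary endpoint (section 6.3, which sets 72 h) nor a listed secondary endpoint (section 6.4).

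The defence does not remove the literal conflict. Reading the 24 hours as the span up to the start of session 2 would settle it, but the protocol never says so.

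**Conclusion.** The contradiction holds. On the protocol's own figures session 2 ends at about 26 h, 2 h past the stated limit, and lies wholly beyond it. This rests on two readings of the text: that the interval is counted from initiation, as written, and that the limit is counted from the same point, since no other starting point is given.

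The consequence is a wrong stopping rule and an inconsistent term for the treatment period, which carries into the CRF completion item and the CRRT instruction. Both sessions would probably be given, and the documents do not support a claim that the 72 h primary endpoint is compromised. The point is worth correcting because a stated rule is wrong as written and the correction is cheap. The heparin point is minor: a missing time unit, which does not make the rules impossible to follow.

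**What to change.** The sponsor should reconcile the duration and cessation paragraphs of section 7.6.4 into one consistent schedule and limit. Which of the two statements is right is for the sponsor and clinical leads to decide. The reconciled text should then be used to:

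1. define the treatment period for this arm, in the same sense in section 7.6.4 (including the CRRT sentence), the flow chart and section 7.9.3;
2. define completed treatment for the CRF item, so that a full course is not logged as a deviation and a partial one is not logged as complete.

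In the same amendment, the sponsor should clarify the time unit of the maintenance heparin figure. No value is proposed here.

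The cost is a few lines of amendment wording, a revised CRF instruction and a note to the two centres. The design, sample size and assessments do not change.

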#### Treatment parameters Mode:

Direct hemoperfusion Inlet

pressure: <250mmHg

Maximum pressure: 500 mmHg

Blood flow rate: 150 ml/min

### **7.6.5 Occurrence of acute renal failure during study period**

#### **Initiation of Renal Replacement Therapy**

Patients with acute renal failure requiring renal replacement therapy will be treated with continuous renal replacement therapy irrespective of their randomization group. Criteria to start CRRT are the following:

- Metabolic acidosis with a pH<7.2
- HCO3 <16mmol/l
- Urine- output <20ml/h
- Uncontrolled hyperkalaemia
- Fluid overload

The oXiris™ product cannot be used in the Standard of Care group nor and Toraymyxin™ treatment group. The hemofiltration in these groups will be performed with the MultiFiltrate™ (Fresenius) and the AV1000S haemofilter or the Prismaflex®-system and the Prismaflex ST150 haemofilter according to our SOP.

#### **Patient medical care after clinical study closure**

After the clinical investigation has been completed, the usual medical care will be given.

## **7.7 Assignment to study treatment**

#### **Randomization**

All eligible patients will be randomly assign to either conventional SOC treatment according to the Surviving Sepsis Campaign Guidelines (27), or SOC treatment with oXiris™ hemofiltration, or SOC treatment with Toraymyxin™ hemoperfusion within 24 hours of admission to the ICU. Patients will be distributed into these 3 groups, in accordance with the randomization table kept in the investigator's office. The randomization list will be performed using a computer generated (simple random number) scheme.

The allocation sequence is concealed in sealed envelopes held at the study centre, which is available 24 hours a day.

According to paragraph 7.5.1 withdrawn patients will be replaced in order to analyse 10 patients per group.

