| Number of Subjects: | 30 patients in total                                                                                                                                                                                                                                                                                                                                                                                                                                                                                                                                                                                                                                                                                                                                                                                                                                                                                                                                                                                                                                                                                                                                                                                                                                                                                                                                                                                                                                                                                                                                                                                                                                |

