## **7 Design of the clinical investigation**

The clinical study design is the following: Pilot,  
Proof of concept,  
Prospective, Open,  
Multi-centre,  
Randomized,  
Controlled trial between three parallel groups

The study is open as the standard of care of septic shock treatment does not include extracorporeal support.

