#### **Treatment allocation**

Treatment allocation will be done according to the usual delivery process. After randomization, the investigator is responsible for completing the randomization list and the accountability documents to record reception of study product.

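### Simple randomisation makes the stated 10 patients per group improbable (2.7%) in this 30-patient, three-arm trial; separately, custody of the list sits badly with the claimed concealment

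*Protocol*

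**What the plan says.** The protocol describes a "Controlled trial between three parallel groups" (section 7), open-label, with "30 patients in total" (synopsis) and two hospitals listed as centres. No allocation ratio is given in words; 1:1:1 is implied by equal group targets.

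Section 7.7, under Randomization, fixes the method: "The randomization list will be performed using a computer generated (simple random number) scheme". It mentions no blocks, no stratification and no cap on arm size. The same section says that "withdrawn patients will be replaced in order to analyse 10 patients per group". Section 7.5.1 also provides for replacement of patients withdrawn after randomisation. Neither place says which arm a replacement enters.

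On custody, patients are allocated "in accordance with the randomization table kept in the investigator's office". The next paragraph says: "The allocation sequence is concealed in sealed envelopes held at the study centre, which is available 24 hours a day". Under Treatment allocation, once a patient has been randomised, "the investigator is responsible for completing the randomization list" together with the device accountability records.

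**The concern.** A fixed number per group and an unrestricted list are two different designs. Simple randomisation fixes the chance of each assignment and leaves the arm sizes random. With only 30 patients in three arms, that randomness is large relative to 10.

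Two things are at stake. The first is precision: section 13 says the pilot exists to supply data for designing later trials, and the smallest arm would supply least. The second is what staff do when the counts drift from 10. If they close full arms, or direct replacements to short ones, upcoming assignments become known in an open trial.

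The location of the table raises a separate question: a sequence described as concealed is also said to sit in the investigator's office.

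**Working it through.** **Inputs.** N = 30 (synopsis); three arms (section 7); 10 per group and a simple list (section 7.7). Assumption: each patient has probability 1/3 for each arm.

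**The plan's own figure.** 30 / 3 = 10, so 10 is the expected arm size. The protocol gives no power calculation to reproduce.

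**Spread of one arm.** SD = √(30 × 1/3 × 2/3) = √6.67 = 2.58 patients.

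**Chance of exactly 10/10/10.** 30! / (10!³ × 3³⁰) = 5.551 × 10¹² / 2.059 × 10¹⁴ = 0.027. Unequal arms therefore have probability 0.973.

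**Other arm sizes.** Summing 30! / (a! b! c! 3³⁰) over all a + b + c = 30:

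| Event | Result |
|---|---|
| All arms 9 to 11 | 0.17 |
| All arms 8 to 12 | 0.41 |
| Smallest arm ≤ 8 | 0.76 |
| Smallest arm ≤ 7 | 0.48 |
| Smallest arm ≤ 6 | 0.25 |
| Largest minus smallest ≥ 6 | 0.43 |
| Expected smallest arm | 7.4 |
| Expected gap, largest minus smallest | 5.3 |

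**Randomising until every arm has at least 10** (simulation, 200,000 runs, no withdrawals): mean 38, median 37, 90th percentile 46, 95th percentile 49. On average this exceeds the stated total of 30 by about 8.

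**Does replacement repair it?** If a replacement takes the next list entry, and withdrawal does not depend on arm, the 30 patients finally analysed follow the same distribution as above. If a replacement takes the withdrawn patient's arm, the final sizes equal those of the first 30 randomised, again with the same distribution. Only steering to the short arm alters the result, and then the assignment is known beforehand.

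**Forcing 10 per arm by closing full arms** (simulation, 200,000 runs, equal chance among open arms): on average 2.9 of 30 assignments are fully determined and a further 4.7 lie between two arms only.

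**Cost in precision.** With equal variances, the standard error of a pairwise difference relative to 10 versus 10 is √[(1/a + 1/b) / 0.2]. For a 7/10/13 split:
- 7 v 10: √(0.2429 / 0.2) = 1.10
- 7 v 13: √(0.2198 / 0.2) = 1.05
- 10 v 13: √(0.1769 / 0.2) = 0.94

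**With blocks.** A single list in blocks of 3, or of 6, gives 10/10/10 at 30, since 30 is a multiple of both. If the sizes vary and a block of 6 is cut after three patients, the gap is at most 2 (two in one arm, none in another). With blocks stratified by two centres (simulation, 50,000 runs per block size, random split of the 30 patients between centres assumed), the largest gap was 2 for block size 3 and 4 for block size 6; the mean gaps were 0.9 and 1.3.

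**The case against.** The best defence is that unequal arms under simple randomisation do not bias the comparison. They cost precision, and in a typical 7/10/13 split that cost is about 10% or less on any pairwise standard error. The trial is a pilot without a power calculation. Simple randomisation is also the least predictable scheme, and blocks in an open trial give some of that up. All of this stands. It limits the seriousness of the point but does not reconcile the scheme with the stated group size.

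Timing also counts. This is version 1.7 of 16.06.2016, for a trial planned from 01/08/2013 to 01/02/2017: 1,050 of 1,280 days, or 82%, had passed. If accrual were linear (an assumption), about 5 of 30 allocations would remain.

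Three stronger readings are tempting, and the protocol does not support them.
- *The scheme can never give 10 per group.* It can, with probability 2.7%. A random ordering of a fixed 10/10/10 list would also do so, though the text does not describe one.
- *Recruiters can foresee the next assignment.* Section 7.7 states that sealed envelopes are used, and nothing shows that enrolling staff can read the table. The investigator's completion of the list is placed after randomisation, so it reads as logging and is no evidence against concealment.
- *Arms will be confounded with centre through different renal replacement systems.* Sections 7.6.4 and 7.6.5 name alternative systems but assign neither to a hospital.

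**Conclusion.** The point holds as an inconsistency within section 7.7. If the list is truly simple with equal probabilities, the stated 10 per group has a 2.7% chance of occurring, an arm of 7 or fewer is about as likely as not (48%), and the replacement rule does not correct this. The allocation method belongs in the protocol, so this is not a detail that can wait for an analysis plan.

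The consequence is a modest loss of precision, concentrated in the smallest arm. Predictable assignments would follow only if arms are closed at 10 or replacements are steered, and the protocol neither states nor excludes this. The figures assume that withdrawal is unrelated to arm. One criterion in section 7.5.1 concerns oXiris circuits only, so the analysed numbers could be further apart.

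On custody, the text is in tension with itself: a table in the investigator's office of an open trial weakens the assurance that sealed envelopes are meant to give. The envelopes are not described as opaque or numbered, and one study centre is named as holder although two hospitals take part. That is a risk to be closed. No failure of concealment has been shown.

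**What to change.** In section 7.7:

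1. Replace the simple scheme by 1:1:1 permuted blocks of undisclosed, randomly varying size (for example 3 and 6) for all remaining allocations. Stratification by centre is optional; it allows the small gaps between arms shown above. If the existing list is in fact a random ordering of a fixed 10/10/10 set, say so instead.
2. State that a replacement takes the next allocation on the list, that no arm is closed at 10, and that no replacement is directed to a chosen arm.
3. Restate 10 per group as a target of about 10, with the expected spread. Without steering, withdrawals will move the analysed numbers away from exact equality even under blocks.
4. Have the list generated and held by someone not involved in enrolment, remove the reference to the investigator's office, and use sequentially numbered opaque envelopes at each centre. The investigator may continue to log the assignment afterwards.

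The cost is amendment wording and a new list; sample size and treatment are unchanged. Blocks bring slight predictability at block ends, limited by varying and undisclosed sizes. Imbalance already accrued stays. If 25 patients had been allocated by a simple list, the SD of an arm would already be √(25 × 2/9) = 2.36, against 2.58 at 30, so late blocking would recover little balance. The custody and replacement rules would still help in full for the patients who remain.
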